**Figure 5. f5:**
[figure not shown]
Household visit and survey timing, and economic data collected
^
38
^. Legend: The blue dot indicates the timing of household visits one (1), two (2), and three (3). Lighter shades of green and red indicate data not collected at visit 1 and 2 respectively. Abbreviations: OOP = out-of-pocket costs; and TB = tuberculosis.

*Study arms and activities*

All participants will complete the survey but receipt of study interventions will depend on which of the four study arms the participant and their household are randomly allocated to (
Figure 6).

**Figure 6. f6:**
[figure not shown]
Study arm allocation (abbreviations: TB = tuberculosis).

In line with our previous research
^
7
^ and BNMT work, during an initial household visit,
*all* participants and their households will receive a basic TB and health educational package delivered by trained BNMT CHS and/or FHCVs and/or a TB survivor where available and a one-off nutritionally-optimised nutritional packages with a value of approximately 3000 Nepalese rupees / 18 GBP. Contents of the packages were previously suggested at a related workshop with in-country stakeholders in Nepal in September 2019
^
11
^.

Participants in support arms will receive either a social support intervention, economic support intervention, or integrated socioeconomic support intervention.
Figure 7 gives further details of activities in each intervention. Interventions will be piloted in approximately 2–3 recruited TB-affected households per study site. ASCOT team members will review the implementation of intervention after this initial pilot and may adapt or refine activities within the intervention. This could include adaptations in dose (e.g. frequency of economic or social support) and mode or mechanism of delivery (e.g. mechanism of economic support could be phone, cash, or bank transfer; social support could be delivered at home, in a community setting, or both). At this “decision point” juncture, the interim progress review findings will be shared with the TSC and a TSC meeting scheduled to discuss these findings. Expectations for cash transfer receipt will be aligned with Nepal NTP strategy goals including regular adherence to TB medication and household contacts attending TB clinics for screening.

**Figure 7. f7:**
[figure not shown]
Intervention activities conducted in each study arm. Abbreviations: ASCOT = the “Addressing the Social Determinants and Consequences of Tuberculosis” project; IEC = Information, Education, and Counselling; NTCC = Nepal National Tuberculosis Control Centre; TB = tuberculosis; UCT = unconditional cash transfer.

Following refinements by BNMT team and TSC inputs, recruitment will proceed. Again, when a study site reaches 32 recruited participants, recruitment will discontinue in that district. This provides ample allowance for completion of intervention activities and three surveys in 32 participants given the predicted attrition rate of ≤10% in the study sites.

The longitudinal survey data detailing participant feedback will form part of the process evaluation of the acceptability and feasibility of the ASCOT intervention. This will be supplemented by real-time self-reported ASCOT project feedback, and time and expense diaries of BNMT implementers, including DPCs and CHS. This data will be further complemented by the enhanced process evaluation aiming to evaluate health systems readiness and scalability of the ASCOT intervention. 

There will be multiple opportunities during the implementation of the pilot trial to assess for any harms or adverse effects. First, the longitudinal survey includes questions related to feedback from participants on the interventions received and involvement in the ASCOT project. Second, after each TB Club is conducted, participants will be asked to provide verbal and written feedback on the activities undertaken during the TB Club, including whether they perceive any of the activities to have caused harm or have the potential to cause harm. Third, issues relating to harm or adverse effects of the ASCOT project are included in the topic guides for KIIs and FGDs. All of these data will be analysed in real-time during the project and discussed between the ASCOT project team and where necessary the TSC to identify if any remediating actions are required. The criteria for discontinuing interventions include: participants who withdraw from the ASCOT project who, as an individual and inclusive of their household, will no longer receive the intervention; harm or adverse effect is identified that is felt by the project team and TSC to preclude continuation of interventions; and acts of God or unforeseen cuts to the study budget curtailing project activities.

**
*Complementary enhanced process evaluation*
**

A process evaluation will use and develop our mixed methods research techniques
^
2,
16,
33,
44
^ including FGDs, KIIs, and a participatory workshop. The process evaluation will also be enhanced and complemented by an assessment of health systems readiness to deliver the ASCOT intervention and potential scalability of the intervention into routine NTP practice in Nepal.

*Health systems readiness and scalability*

Even effective interventions will
*not* have impact unless they can be scaled-up and integrated into organizational practices such as care pathways, and normalised into health professionals’ routine practice
^
45
^. The process evaluation will include both a health systems readiness and scalability assessment. The concept of scalability is relatively new in implementation science
^
46
^. It is often thought to be interchangeable with the ability to widen the reach of an intervention. However, there are many more considerations and a lack of attention given to how the intervention will perform under routine conditions or the extent to which it is embedded in a local delivery system will hinder not only the implementation but also the possibility for scale-up. Therefore, it is of paramount importance to assess the potential to scale-up early in the process
^
47
^. Prior to the FGDs and KIIs below, we will develop a brief questionnaire encompassing elements of both health systems’ readiness and scalability assessment, which will be conducted with relevant stakeholders prior to their participation in FGDs and KIIs. Ultimately, the questionnaire, FGD, and KIIs will collate key stakeholders’ perceptions of the in-country capacity to translate the knowledge generated from ASCOT into policy and routine practice.

*Normalization Process Theory (NPT)*
^
48
^

NPT will be used to inform the design of FGDs and KIIs and support both health system readiness and scalability assessment. The NPT and NoMAD tool
^
49
^ describe four constructs through which stakeholders implement and integrate a new practice into their work: coherence (or sense-making); cognitive participation (or engagement); collective action (work done to enable the intervention to happen); and reflexive monitoring (formal and informal appraisal of the benefits and costs of the intervention)
^
48
^. Feeding into health systems readiness and scalability assessment, these four constructs will form the backbone of our FGD and KII topic guides (see Extended data
^
19
^).

*Recruitment of multisectoral stakeholders*

The stakeholder populations are described above. In brief, the subset of people with TB recruited to the pilot trial will be invited to participate in an FGD and workshop at either household visit 2 or 3. As has worked well in Nepal during our previous research, the other purposively selected stakeholder groups will be invited to participate in an FGD or KII, and workshop by phone, email, and/or in person. The discrete consent forms and participant information sheets (PIS) for different participant groups and ASCOT activities can be found in the Extended data
^
19
^.

*Brief questionnaire*

Prior to participation in FGDs, NTP managers, NTP TB clinic staff, social protection specialists, and ASCOT DPC, CHS and FCHV participants will be asked to complete the brief questionnaire concerning health systems readiness and scalability detailed above. People with TB will not be asked to complete this questionnaire.

*FGDs*

FGDs will be semi-structured and incorporate open-ended questions informed by the work above and topic guides piloted amongst the ASCOT team and in an initial FGD. During the first FGD section, questions will relate primarily to the socioeconomic impact of TB, current (e.g. support for people with DR-TB) and potential socioeconomic support interventions for TB-affected households, and the household level and health systems level challenges to the NTP of delivering them.

The FGDs will be conducted with separate groups of approximately five key stakeholders. Stakeholders will be invited to participate according to their background (e.g. people with TB will be asked to participate in one FGD, and NTP staff will be asked to participate in another separate FGD). The second section of the FGD will include a presentation of the elements that constitute the ASCOT intervention and participants will be asked to discuss their opinions on its potential. Participants who have experienced the intervention, including people with TB diagnosed by ACF or PCF and randomised to an intervention arm, will be asked to discuss their opinions on its successes, challenges, and/or failures, and consider how to refine the intervention to overcome the issues raised. ASCOT DPCs, CHS, and FCHV will be asked to also consider the reasons for non-participation and drop-out amongst the people with TB invited or recruited to participate in their district.

We will perform member checking in each FGD by noting key points of the discussion, summarizing these points on a wall chart, and clarifying their accuracy with the group. Formal field notes may also be taken. Based on our previous work, it is predicted the FGDs will last between 90 and 120 minutes. The FGDs will be moderated by members of the project team trained in qualitative methods including conducting FGDs. The ASCOT field team will support FGDs with people with TB in order to facilitate any dialectic interpretation or contextual explanations. The discussions will be audio recorded in Nepali language, translated into English, and back-translated by an independent translator who is not part of the project team.

*KIIs*

Participants who occupy higher-level positions in terms of policy-making and leadership in either the NTP or social protection programmes in Nepal, will be invited to participate in KIIs. This is in line with our previous research methods, which found attendance and engagement of these participants to be higher for KIIs than FGDs. Given that most of the higher-level agencies, institutions, and leaders are based in Kathmandu, it is likely that this is where the majority of KIIs will take place. Participants will be able to choose the location that suits them best or a location organised by the ASCOT Project Manager. The KIIs will be conducted by the Project Manager and Co-investigator (in Nepali or English) and Chief Investigator (in English) where appropriate. Topic guides for KIIs and subject matter will be parallel to the FGDs described above. 

*Workshop and dissemination meeting*

The final activity will be a one-day workshop bringing together the 40 key stakeholders. The morning section of the workshop will consist of interactive presentations from the project team and stakeholder group representatives, and discussions exploring the preliminary findings of the ASCOT survey, pilot trial, and mixed-methods process evaluation. The afternoon section of the workshop will consist of multi-sectoral working groups (≤10 diverse stakeholders) developing recommendations for refinements of the intervention and considerations ahead of application for funding for the large-scale, well-powered ASCOT trial.

**
*Randomisation and blinding*
**

In order to randomise participants into study arms, a random number table will be prepared prior to recruitment by two ASCOT team members (KD, BR). A screenshot will be taken documenting the time and date of the random number table generation in order to improve transparency and reduce the chances of contaminated randomization or tampering. The table will be saved centrally and only accessible by the Project Manager (BR) and no other ASCOT team members.

The random number table will randomise participants 1:1:1:1 to the four study arms (social, economic, socioeconomic, and control arms) in blocks of 32 in each of the four study site districts according to site-level participant identification code. Once participants have given informed consent, been recruited, and given a site-level code, the ASCOT field team member who consented the participant will call the Project Manager (BR) and be informed by either KD or BR to which arm the participant has been allocated.

Digital randomisation using an online programme was originally considered but perceived as inappropriate and unfeasible in the study setting.

It will not be possible to blind participants or ASCOT field team members delivering the interventions (DPC, CHS, FCHV) to the randomisation. However, NTP staff will not be informed of the arm to which participants are randomised.

### Outcomes to be measured

**
*Co-primary outcomes*
**

The co-primary outcomes of the ASCOT pilot trial are acceptability and feasibility of the social, economic, and socioeconomic support interventions.

*Feasibility* will be measured using quantitative data including:

i) Recruitment (e.g. number of people invited, recruited, and participant attrition);ii) Fidelity to survey completion and the intervention (e.g. adherence to and completion of socioeconomic support delivery including receipt of cash transfers and attendance at TB Club amongst intervention arm participants); andiii) ASCOT staff time and costs plus overall project costs.

*Acceptability* will be measured using mixed-methods including:

i) Quantitative analysis of the implementer and participant satisfaction form;iii) Thematic analysis of the qualitative FGD and KII data within Sekhon’s Framework for healthcare interventions and quantitative analysis of the brief questionnaire completed prior to FGDs will include evaluation of health systems readiness and scalability
^
50,
51
^.

**
*Secondary outcomes*
**

Unpowered, exploratory secondary outcomes will compare the proportion of people with TB in each study arm by rates of:

*TB treatment success:* NTP-defined outcome of completed TB treatment or confirmed cured documented in TB register.
*Catastrophic costs:* TB-affected households that incur total out-of-pocket expenses and lost income during TB illness that equated to more than 20% of the same household’s annual pre-TB income.
*Wellbeing:* measured by self-reported levels of stigma, depression, and quality of life at six-month follow-up adjusted for baseline.

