## Abstract

**BACKGROUND: **The World Health Organization’s End TB (tuberculosis) Strategy advocates social and economic support for TB-affected households but evidence from low-income settings is scarce. We will evaluate the feasibility and acceptability of a locally-appropriate socioeconomic support intervention for TB-affected households in Nepal.

**METHODS: **We will conduct a pilot randomised-controlled trial with mixed-methods process evaluation in four TB-endemic, impoverished districts of Nepal: Pyuthan, Chitwan, Mahottari, and Morang. We will recruit 128 people with TB notified to the Nepal National TB Program (NTP) and 40 multisectoral stakeholders including NTP staff, civil-society members, policy-makers, and ASCOT (Addressing the Social Determinants and Consequences of Tuberculosis) team members. People with TB will be randomised 1:1:1:1 to four study arms (n=32 each): control; social support; economic support; and combined social and economic (socioeconomic) support. Social support will be TB education and peer-led mutual-support TB Clubs providing TB education and stigma-reduction counselling. Economic support will be monthly unconditional cash transfers during TB treatment with expectations (not conditions) of meeting NTP goals. At 0, 2, and 6 months following TB treatment initiation, participants will be asked to complete a survey detailing the social determinants and consequences of TB and their feedback on ASCOT. Complementary process evaluation will use focus group discussions (FGD), key informant interviews (KII), and a workshop with multi-sectoral stakeholders to consider the challenges to ASCOT’s implementation and scale-up. A sample of ~100 people with TB is recommended to estimate TB-related costs. Information power is estimated to be reached with approximately 25 FGD and 15 KII participants.

**CONCLUSIONS:** The ASCOT pilot trial will both generate robust evidence on a locally-appropriate, socioeconomic support intervention for TB-affected households in Nepal and inform a large-scale future ASCOT trial, which will evaluate the intervention’s impact on catastrophic costs mitigation and TB outcomes.

The trial is registered with the ISRCTN (
ISRCTN17025974).

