^. The Seed Award research used mixed methods to characterise the socioeconomic impact and barriers to accessing TB diagnosis and care in Nepal and to support design of potential interventions to overcome these issues
^
12
^. The Seed Award was housed within the “
IMPACT-TB” active-case finding study in Vietnam and Nepal (EU-Horizon 2020, grant 733174).

Both the Seed Award and IMPACT-TB were implemented by a well-established Nepalese NGO, Birat Nepal Medical Trust (
BNMT), with over 50 years of experience in implementing public health interventions in Nepal. IMPACT-TB and the Wellcome Seed Award research found that catastrophic costs were experienced by 61% of TB-affected households
^
13
^ and identified distinct socioeconomic factors impeding access to TB services (
Figure 1)
^
14
^. Focus group discussions (FGDs) characterised where along the patient pathway from TB symptoms to care seeking, diagnosis, treatment, and treatment outcome, support interventions could be delivered (
Figure 2). The research also demonstrated that people with TB in Nepal commonly experienced self-stigma
^
15
^ and exploratory analyses suggested that experiencing stigma was associated with catastrophic costs and worse TB treatment outcomes
^
16
^.

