### Study setting

Nepal is a lower middle-income country with a TB incidence of 245/100,000 people per year
^
23
^. Moreover, TB is the seventh leading cause of death in Nepal
^
24
^. Multi-drug resistance (MDR) rates are low in new cases but affect approximately 1 in 7 people being retreated for TB. Rates of treatment success are over 90% but lower for people with MDR-TB (70%) and very low for people with HIV-TB co-infection (9%). Treatment coverage is 70% indicating difficulties with access to TB services. This is compounded by stigma and discrimination towards people with TB and self-stigmatisation, which have been found to be prevalent in cohort studies in Nepal
^
14,
15,
25
^.

The National Tuberculosis Program (NTP) strategy focuses on a biomedical approach to address TB, including recent advances in expanded access to molecular diagnostic tests such as Xpert MTB/RIF
^®^
^
24
^. Nevertheless, despite free basic TB diagnostic tests and medicines and financial support for people with MDR-TB, more than half of TB-affected people experience catastrophic costs (defined as total TB-related costs and lost income >20% of a household’s annual income) of TB illness and care seeking in Nepal. Such costs include travel for Directly Observed Therapy (DOT), expenses for additional nutrition, and loss of income, and can lead to lower rates of TB treatment success, especially amongst underserved households
^
13,
25–
27
^. To address this, Objective 1 of the Ministry of Health and Population National TB Control Centre’s National Strategic Plan to End Tuberculosis in Nepal, 2021–2026 is “to strengthen the health system and improve quality TB services under universal health coverage and ensure no TB-affected family faces catastrophic costs due to TB by 2025”.

Fewer than one in two people in Nepal are covered by a basic social protection floor and one in four live in poverty
^
28
^. Despite widespread use of DOT, greater GeneXpert coverage, and intensified case finding, TB services in Nepal are challenged by significant geographical barriers, including mountains, flooding, landslides, and poor road infrastructure, all of which can hamper TB prevention and treatment outcomes
^
24,
26–
29
^. The Nepal NTP provides 3,000 Nepalese Rupees (~27 USD) monthly cash transfers to people with MDR-TB receiving ambulatory care, nominally for nutrition and transport
^
24
^. People with drug-sensitive TB (DS-TB) do not currently receive any financial support in Nepal
^
11
^.

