**Secondary exploratory outcomes analyses**

Key quantitative survey data will include TB-related costs, stigma, mental health, and quality of life. This will be supplemented by TB treatment outcome data from the National TB Program register.

As per our related research, WHO TB Patient Costs Survey methods will be used to calculate total direct costs, lost income, and catastrophic costs (total TB-related costs of more than 20% of the same household’s annual pre-TB income)
^
38
^. TB treatment outcomes will be collated from National TB Program registers and will be aggregated to TB treatment success (the sum of the National TB Program defined outcomes of “Treatment completion” and “Cure”) vs no TB treatment success (the sum of all other National TB Program defined outcomes including “Lost to follow-up”, “Death”, “Treatment Failure”, “No evaluation”, “Change to drug-resistant TB regimen” and “Transferred out”).

Stigma will be measured by locally developing stigma score for the Nepali context by adapting elements of the validated Van Rie stigma scale, which comprises ten stigma-related questions with 5-point Likert scale responses. Each response category of the scale will be assigned scores of: -2: strongly disagree, -1: disagree; 0: neither agree nor disagree; +1: agree, and +2: strongly agree. The total scores will range from -20 (no stigma) to +20 (highest levels of stigma). A threshold of equal or above the median cohort stigma score will also be used as a binary classification of stigma.

Mental health will be measured using an adapted version of the Patient Health Questionnaires, PHQ-9, which has been validated in Nepal. The tool explores anxiety, depression, wellbeing, and discrimination through nine questions with four-point scale responses of 0: not at all, 1: sometimes, 2: usually, and 3: always. The range of scores is from 0 to 27 and the following categorisations have been used in the validated tool: 1–4 minimal, 5–9 mild, 10–14 moderate, 15–19 moderately severe, and 20–24 severe depression level. A threshold score of equal or above 10 will also be used as a binary classification of depression.

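### The catastrophic-cost indicator, as written, does not deduct the trial's own cash transfers, so it may miss their direct effect or move against the arms that receive them; report it both with and without deduction

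*Protocol article*

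**What the plan says.** The protocol article gives the definition twice. Under Outcomes to be measured, the secondary outcome is "TB-affected households that incur total out-of-pocket expenses and lost income during TB illness that equated to more than 20" per cent, with the household's yearly income before TB as the denominator. Under Secondary exploratory outcomes analyses it is "total TB-related costs of more than 20% of the same household’s annual pre-TB income", and the calculation is referred to a cited method: "WHO TB Patient Costs Survey methods will be used to calculate total direct costs, lost income, and catastrophic costs". Neither place mentions money received by the household.

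The Study setting section says what the costs contain: "Such costs include travel for Directly Observed Therapy (DOT), expenses for additional nutrition, and loss of income". The Abstract describes the economic component: "Economic support will be monthly unconditional cash transfers during TB treatment". Cash goes to the economic arm and the combined arm only. A one-off nutritional package goes to every participant (Study arms and activities), so it does not differ between arms.

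The outcome is labelled unpowered and exploratory. The proportion above the threshold is nevertheless to be compared across arms with a chi-squared test at p<0.05. The Abstract and the Discussion name catastrophic costs as an outcome of the planned larger trial.

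**The concern.** A cash transfer can protect a household in two ways. It can pay part of the bill directly, or it can change behaviour so that the bill is smaller, for example by less income being lost. Read literally, the formula sees only the second. The numerator is expenses plus lost income, with nothing subtracted. The denominator is income before TB, which the trial cannot change. At the same time, cash spent on extra food or on travel to treatment enters the numerator as a TB cost, and only the arms that receive cash have that extra money to spend.

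Assessing the effect on catastrophic costs is one of the pilot's stated exploratory aims, and the pilot is meant to inform the design of the larger trial. An arm-level estimate that leaves out the direct effect, or has the opposite sign because of how the cash was spent, could be misread as the cash component failing.

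**Working it through.** **Inputs from the document.** Threshold: 20% of annual pre-TB income. Background rate: "catastrophic costs were experienced by 61% of TB-affected households" (Introduction). Treatment length: a standard six-month course (Household visits and surveys). Arm size: 32.

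**Inputs not in the visible text.** The ASCOT transfer amount and household incomes. As a stand-in only, I take the existing programme payment as the upper value: "The Nepal NTP provides 3,000 Nepalese Rupees (~27 USD) monthly cash transfers to people with MDR-TB". The range is NPR 1,500 to 3,000 a month for six months, so T = 9,000 to 18,000.

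**Formulae.** Let C be counted costs without any transfer, Y pre-TB income, s the share of T spent on additional counted items, and d the reduction in lost income or other counted costs that the transfer brings about.
- As written: catastrophic if C + sT − d > 0.2Y. The transfer helps only if d > sT. If d = s = 0 it has no effect.
- Net of transfers: catastrophic if C + sT − d − T > 0.2Y. The transfer helps whenever d + (1 − s)T > 0, even if behaviour does not change at all.
- If lost income is calculated from income during treatment and that income includes the transfer, the as-written numerator already contains −T. A further subtraction would deduct the transfer twice (−2T).

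**Which households change class.** With s = d = 0, netting reclassifies those with C/Y above 20% and up to 20% + T/Y. At T = 18,000:
- Y = 90,000: 18,000/90,000 = 20%, so the band is 20–40%.
- Y = 180,000: 18,000/180,000 = 10%, band 20–30%.
- Y = 360,000: 18,000/360,000 = 5%, band 20–25%.

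Example: at Y = 180,000, costs of 30% are 54,000, and 54,000 − 18,000 = 36,000 = 20.0%, just no longer above the threshold. At 31%, 55,800 − 18,000 = 37,800 = 21.0%, and the household is catastrophic under both versions.

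The other direction: at Y = 180,000, s = 0.5, d = 0, the numerator rises by 9,000, or 5% of income. Households otherwise above 15% and up to 20% are then newly counted as catastrophic in the cash arms.

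**Illustrative rates.** Simulated households, with lognormal income (median NPR 100,000 to 300,000, log-SD 0.7), lognormal cost-to-income ratio (log-SD 0.8 or 1.2) set so that 61% of controls exceed 20%, T = 9,000 or 18,000, and d = 0. Rates in an arm receiving cash:

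| Share s spent on counted items | Without deduction | Net of transfers |
|---|---|---|
| 0 | 61% | 29–56% |
| 0.25 | 63–75% | 34–57% |
| 0.5 | 64–85% | 41–58% |
| 1 | 68–95% | 61% |

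The control rate is 61% throughout. For intermediate s the two versions lie on opposite sides of it.

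**Power.** For two arms of 32, power is about 25% for 61% versus 45%, and 11% for 61% versus 70%. The pilot would rarely declare either direction significant. The risk lies in how the estimate is read.

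**The case against.** The strongest objection is that a gross definition is inferred from silence. No section says that transfers are ignored. The calculation is handed to WHO survey methods that are not shown, and the full protocol, operating procedures and survey instrument are listed as extended data. If income during treatment includes the transfer, lost income already absorbs it. This stands, and the point is therefore conditional on that method.

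A reader might also infer that the economic arms cannot show a benefit by definition. The document does not support that: under the as-written formula a benefit appears whenever d exceeds sT. The Introduction reports that the team's earlier intervention in Peru mitigated catastrophic costs, although how that study treated transfers cannot be seen here.

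The magnitude is hypothetical. The NPR 3,000 figure is the national programme's MDR-TB payment and not the trial's, and no household income is given. This stands in full.

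The net version has its own built-in result. It subtracts money only in the arms that are paid, so the rate falls to 29–56% at s = 0 with no change in behaviour. It is therefore not a neutral replacement for the indicator as written.

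Finally, the outcome is exploratory, the co-primary outcomes are feasibility and acceptability, and the survey also records food insecurity, coping strategies and continuous costs. No section says that the pilot's difference will supply the larger trial's effect size. These points limit the weight of the concern. They do not resolve how the indicator should be read between arms.

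**Conclusion.** The concern holds in a conditional form. As written, the indicator deducts no ASCOT cash, sets costs against a fixed pre-TB income, and rests on a list of costs that includes additional nutrition and treatment travel. Unless the cited WHO method already counts the transfer in income during treatment, the indicator does not register the direct offset, and it can move against the economic and combined arms if cash goes on counted items. Benefit through smaller income loss or other savings remains possible.

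The actual size cannot be calculated from the visible text. The simulated ranges rest on assumed transfers, incomes and spending shares with no behavioural benefit. They show only that the choice of version can change the direction of the comparison. The co-primary outcomes are untouched. The change is worth making because this indicator serves a stated aim and is carried forward to the larger trial.

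**What to change.** 1. State whether ASCOT transfers are counted in household income during treatment when lost income is calculated. If they are, do not subtract them again.
2. Report the exploratory indicator in all four arms in two versions: without deduction, as now defined, for comparison with other surveys; and net of ASCOT transfers actually received. If transfers turn out to be inside income during treatment, the version without deduction must be calculated with them taken out of that income.
3. Show nutrition and travel costs separately by arm, so that a rise caused by spending the transfer is visible.
4. Say in the plan that neither version alone is evidence of mitigation or of its absence, and that the net version counts the payment itself as benefit.

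Receipt of cash transfers is already recorded as a feasibility measure, so this needs one derived variable and no new data collection. The downside is two figures to report and explain instead of one.
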